A dose escalation protocol will be used to determine the lowest radiotherapy dose that can safely achieve sympathetic downregulation. This protocol will involve 13 patients with the doses escalated as follows: The first 3 patients would be treated at 8 Gy per fraction for 3 fractions on alternate days. If no serious adverse events occur then we will increase the dose to 9 Gy per fraction for 3 fractions on alternate days in the next 3 patients, 10 Gy per fraction for the next 3 patients for 3 fractions on alternate days and 11 Gy per fraction for 3 fractions on alternate days for the final 4 patients (figure 2). There will be a minimum of 6 weeks between the last participant treated at each dose before escalation the next dose to allow for detection of adverse events at participants' 6 week follow up visit. Before each dose escalation we will have an independent safety committee review all patient data and radiotherapy doses will only be escalated if there are no safety concerns.

Our study is a safety study, and we are powered to detect serious adverse events as our primary endpoint. Serious adverse events (SAEs) defined as any related and unexpected grade 3 toxicity requiring hospitalization, grade 4 toxicity or grade 5 toxicity as defined by the common terminology criteria for adverse events.

If a serious adverse event occurs, then no further fractions would be given to that patient and the dose would be reduced by 1 Gy for all subsequent patients (up to a total of 13 patients) without further dose escalation. If an SAE occurs at the lowest radiotherapy dose (8 Gy per fraction for 3 fractions) all subsequent patients will receive treatment at the even lower dose of 7 Gy per fraction for 3 fractions, if approved by our independent safety committee. However as highlighted in section 5 we have chosen a starting dose within the safe upper limit for neuronal tissue, so we do not anticipate this. An early stopping rule will be set to halt enrolment if 4 out of the first 8 patients develop and SAE. If patients withdraw from this trial then they will be replaced, and the study will continue until 13 patients have completed the dose escalation protocol (as detailed in section 9.8). We will not recruit any extra participants into our dose escalation protocol, unless participants withdraw, in which case they will be replaced. Once 13 participants complete the dose escalation protocol no further patients will be recruited.

Figure 2.

[figure not shown]

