### Visits 4 to 6 – Hypofractionated radiotherapy to the stellate ganglia

Over the course of one-week, patients will undergo up to 3 fractions of hypofractionated radiotherapy targeted bilaterally to the lower half of the stellate ganglia and T1-2 paravertebral chain (60 minutes).

Prior to each fraction of radiotherapy blood samples (approximately 16 ml) will be taken to monitor plasma levels of NPY and other biomarkers. Routine blood tests (including renal function, full blood count and thyroid function) will also be checked prior to the first fraction of treatment. Blood samples will be labelled with the participants' study number and stored for analysis. All stored samples will be de-identified and will only be identified by a study specific participant number and will be destroyed after processing, unless participants have specifically consented to have their samples stored for use in future studies (10 minutes)

Before and after each fraction of radiotherapy a cardiovascular examination and neurological examination will be performed by one of the study doctors paying attention to signs of Horner's syndrome

(ptosis and pupil constriction) or upper limb sensory impairment. Cardiovascular observations including postural blood pressures and heart rate will be recorded, and an electrocardiogram will be performed. New postural hypotension defined as a symptomatic postural blood pressure drop of 20mmHg will be considered significant. (10 minutes each) If any serious treatment related adverse events are detected, then no further fractions of radiation will be delivered to that patient.

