### **9.8. Early Discontinuation/Withdrawal of Participants**

During the course of the study a participant may choose to withdraw early from the study treatment at any time. This may happen for several reasons, including but not limited to:

- The occurrence of what the participant perceives as an intolerable AE.
- Inability to comply with study procedures
- Participant decision

Participants may choose to stop treatment and/or study assessments but may remain on study follow-up.

Participants may also withdraw their consent, meaning that they wish to withdraw from the study completely.

According to the design of the study, participants may have the following three options for withdrawal;

- 1) Participants may withdraw from active follow-up and further communication but allow the study team to continue to access their medical records and any relevant hospital data that is recorded as part of routine standard of care; i.e., Remote monitoring of their ICD.
- 2) Participants can withdraw from the study but permit data and samples obtained up until the point of withdrawal to be retained for use in the study analysis. No further data or samples would be collected after withdrawal.
- 3) Participants can withdraw completely from the study and withdraw the data and samples collected up until the point of withdrawal. The data and samples already collected would not be used in the final study analysis. A limitation to this withdrawal would be any data that has already been used as part of interim analysis, including by the independent safety committee.

In addition, the Investigator may discontinue a participant from the study treatment at any time if the Investigator considers it necessary for any reason including, but not limited to:

- Pregnancy
- Ineligibility (either arising during the study or retrospectively having been overlooked at screening)
- Significant protocol deviation
- Significant non-compliance with treatment regimen or study requirements
- Clinical decision

The type of withdrawal and reason for withdrawal will be recorded in the CRF.

Withdrawn participants will be replaced

Patients who have withdrawn from the study who also opt out of further study follow up will continue to be followed indefinitely up as part of their routine clinical care. This will include follow up under the device clinic, and where applicable by the heart failure and arrhythmia service.

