#### **10.5. Follow-up of Serious Adverse Events**

In the event of an SAE, participants will remain under study follow up for the duration of the study to monitor the progress of the SAE. If deemed clinically appropriate by the investigators, and with the consent of the patient, onward clinical referral to the appropriate clinical specialty will be arranged for further investigation and treatment of symptoms. This study will monitor and report on SAE which occur within the pre-specified monitoring window period as discussed in section 10.0. Following completion of the study, all patients will return to routine clinical follow up as part of their routine clinical care. This will include follow up under the device clinic and, where applicable, by the heart failure and arrhythmia service.

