#### **11.2. Description of the Statistical Methods**

To measure our primary safety endpoint, we will measure the frequency of adverse events in the 6 months post radiotherapy. Our trial is powered to detect adverse event rates of 34% (see below)

For secondary outcome measures such as changes in circulating biomarker levels (NPY) and changes in number of device therapies following radiotherapy we will use non-parametric tests such as a Wilcoxon signed rank test to determine if changes are statistically significant.

To assess correlation between changes in biomarker levels and number of device therapies we will use a correlation matrix using non-parametric correlation tests such as Spearman rank-order correlation.

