#### **11.4. Analysis populations**

All participants who completed their course of radiotherapy bilaterally to the stellate ganglia (an adverse event analysis).

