#### **11.6. Stopping rules**

An early stopping rule will be set to halt protocol enrolment if  $\geq 4$  of the first 8 participants developed a related and unexpected SAE.

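### Section 11.4 limits the adverse event analysis to patients who completed radiotherapy, although an SAE stops treatment, so read literally it drops some patients because they had the primary endpoint event

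*Protocol*

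**What the plan says.** Section 11.4 names one population, "All participants who completed their course of radiotherapy bilaterally to the stellate ganglia (an adverse event analysis". Section 11.1 states that no separate SAP is in use, so 11.4 is the operative text.

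The planned course is three fractions on alternate days (sections 7 and 9.4.1). Two places stop it after a serious event:
- Section 7: "If a serious adverse event occurs, then no further fractions would be given to that patient".
- Section 9.6, Visits 4 to 6: "If any serious treatment related adverse events are detected, then no further fractions of radiation will be delivered to that patient".

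The other safety provisions are not limited to completers:
- Section 6 measures the primary endpoint during the radiotherapy sessions as well as at the visits up to 6 months, and section 10 opens the reporting window at the first fraction.
- Section 10.5 says that after an SAE "participants will remain under study follow up for the duration of the study".
- The stopping rule in 11.6 counts SAEs among participants: four or more "of the first 8 participants developed a related and unexpected SAE".

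On numbers, section 7 says "the study will continue until 13 patients have completed the dose escalation protocol" and section 9.8 says "Withdrawn participants will be replaced". Section 11.2 describes the primary analysis with the words "we will measure the frequency of adverse events in the 6 months post radiotherapy".

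**The concern.** Membership of the primary safety set depends on the outcome that the set is meant to measure. A patient with a treatment-related SAE after fraction 1 or 2 gets no further fractions, so does not complete the three-fraction course, and under 11.4 leaves both the numerator and the denominator of the SAE rate. That rate is what sections 11.3 and 11.7 compare with 34%.

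The design also looks for such events. Sections 9.4.1 and 16.4.1 justify splitting the dose partly as a way of detecting complications before denervation is permanent, and section 10 counts the treatment period among the times when denervation effects may show. Monitoring and final analysis would then use different denominators: participants in 11.6, completers in 11.4.

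At stake is the trial's primary result. With 13 patients, one SAE more or less can decide it.

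**Working it through.** **The plan's own figure.** Section 11.3 gives 13 patients for a one-sided, one-sample test of proportions with alpha 0.05, power 80% and rates of 9% and 34%. The normal approximation with null 9% and alternative 34% gives

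n = [1.645·√(0.09·0.91) + 0.842·√(0.34·0.66)]² / 0.25² = 12.09, so 13.

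The figure reproduces in that direction. With the null at 34%, which is the stated aim of showing a rate not above 34%, the same formula gives 16.65, so 17. That is a separate matter. The check below takes 13 as given and looks only at who is counted.

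**Decision rule.** The protocol does not say whether the test is exact; an exact binomial test of 34% is assumed. The largest number of SAEs that still passes is:
- 1 for n = 12 or 13: P(X ≤ 1) = 0.0491 and 0.0347.
- 0 for n = 8 to 11.
- none for n ≤ 7, since 0.66⁷ = 0.055.

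With all 13 treated patients analysed, the exact size is therefore 0.035.

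**Completer rate.** Let s be the share of SAEs that occur before the last fraction and so stop treatment. The protocol gives no value, so s is ranged. If the true rate among treated patients is 34%:
- the probability that a treated patient is stopped by an SAE is 0.34s;
- the SAE rate among completers is p_c = 0.34(1 − s)/(1 − 0.34s).

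**False-pass probability.** With 13 treated and no replacement, the number of completers n is binomial(13, 1 − 0.34s). The probability of wrongly passing is the sum over n of P(n)·P(X ≤ limit(n) | n, p_c).

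| s | 0.34s | p_c | Expected stopped, of 13 | False pass |
|---|---|---|---|---|
| 0 | 0 | 0.340 | 0 | 0.035 |
| 5% | 0.017 | 0.329 | 0.22 | 0.044 |
| 10% | 0.034 | 0.317 | 0.44 | 0.053 |
| 25% | 0.085 | 0.279 | 1.1 | 0.079 |
| 50% | 0.170 | 0.205 | 2.2 | 0.148 |

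These figures hold the SAE rate at 34% throughout. They ignore the dose reduction after an SAE and the early stopping rule.

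**Single-trial example (assumed data).** 13 treated, 2 SAEs, one of which stops treatment:
- As 11.4 is written: 1/12, p = 0.66¹² + 12·0.34·0.66¹¹ = 0.0068 + 0.0422 = 0.049, which passes.
- All treated: 2/13, p = 0.0045 + 0.0302 + 0.0933 = 0.128, which does not pass.

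**The opposite direction (assumed data).** 13 treated, 1 SAE in a completer, and two event-free patients who leave before fraction 3 for reasons listed in 9.8:
- As 11.4 is written: 1/11, p = 0.069, which does not pass.
- All treated: 1/13, p = 0.035, which passes.

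**The case against.** **The wording can be read more kindly.** Visits 4 to 6 set three fractions as a maximum, so a course ended by the protocol's own rule might count as that patient's completed course. The label in 11.4 and the follow-up in 10.5 also suggest no wish to discard these patients. This shows that the omission may not be intended. It remains the likelier reading, because elsewhere the course is three fractions and no other text brings these patients back.

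**Few SAEs may fall in the treatment week.** Section 10 expects denervation effects during treatment or in the days, weeks or months after it, and dose-limiting toxicity within 6 weeks of completion. Only events before fraction 3 are lost. Nothing supports a large s, and at 10% the false-pass probability is about the nominal 0.05. This stands and limits the size. The two-SAE example also sits close to the threshold. With a single SAE that stops treatment, 0/12 (p = 0.007) and 1/13 (p = 0.035) both pass.

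**Replacement.** A reader might infer that stopped patients are replaced until 13 have completed, which gives larger false-pass figures: 0.050, 0.086 and 0.221 at s = 10%, 25% and 50%. The text does not support this as the main case. Sections 7 and 9.8 replace participants who withdraw, and a patient stopped for an SAE stays under follow-up.

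**Direction.** A reader might infer that the error always flatters safety. That is true for SAE-stopped patients only; the last example above runs the other way.

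**Oversight.** A reader might infer that patients are less well protected. They are not: the safety committee reviews all patient data before each escalation, and 11.6 counts participants. The effect is confined to the final reported rate.

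**Section 11.2.** Its time window could be taken as a second defect. It is probably shorthand, since sections 6 and 10 state the window clearly, and as the plan stands it changes no SAE result.

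**Conclusion.** The point holds. Read literally, 11.4 excludes patients from the primary SAE rate because of the primary endpoint event, against the endpoint definition in section 6, the reporting window in section 10 and the follow-up in 10.5. That exclusion lowers the rate, while excluding event-free non-completers raises it. A completer set is the wrong primary population for safety in either case.

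The size is uncertain and may be modest. The false-pass probability of 0.035 becomes 0.044 to 0.053 for s of 5% to 10%, and 0.079 to 0.148 for s of 25% to 50%. These figures assume a true rate of 34%, an exact test, 13 treated, no replacement and no change of dose; s itself is an assumption. In a trial this small, one excluded patient can still reverse the conclusion. The correction should be made before the primary analysis.

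**What to change.** In 11.4, write: *Safety population: all participants who received at least one fraction of radiotherapy.* Keep completers as a supportive set. State that participants whose treatment is stopped, or who are replaced, stay in the safety population unless they withdraw their data under option 3 of section 9.8.

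As a consequential edit, align 11.2 with section 10: count events from the first fraction until 6 months after the last fraction received. Once stopped patients are in the population, a window that opens only after radiotherapy could leave out the SAE that stopped them.

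The cost is a short rewording of 11.4 and one sentence in 11.2. Adverse events are already assessed at Visits 4 to 9 (Appendix A), and 10.5 already requires follow-up after an SAE. No visit, dose rule or sample size changes.

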#### **11.5. Decision points**

Interim analysis will be performed after the completion of each dose of the dose escalation protocol. This will include assessment of safety by an independent safety committee. Study investigators will respect any recommendations from the safety committee, including a recommendation to stop the trial if there is sufficient safety concern.

#### **11.6. Stopping rules**

An early stopping rule will be set to halt protocol enrolment if  $\geq 4$  of the first 8 participants developed a related and unexpected SAE.

#### **11.7. The Level of Statistical Significance**

We are 80% powered to demonstrate a SAE rate not exceeding 34% (range 9-34%) on a one sided, one sample test for proportions (alpha 0.05).

### **12. DATA MANAGEMENT**

The plan for the data management of the study are outlined below. There is not a separate Data Management document in use for the study. Participant data will be treated the same way irrespective of the outcome of the initial screening assessment.

#### **12.1. Source Data**

Source documents are where data are first recorded, and from which participants' CRF data are obtained. These include, but are not limited to, hospital records (from which medical history and previous and concurrent medication may be summarised into the CRF), clinical and office charts, laboratory and pharmacy records, diaries, microfiches, radiographs, and correspondence.

CRF entries will be considered source data if the CRF is the site of the original recording (e.g. there is no other written or electronic record of data). All documents will be stored safely in confidential conditions.

On all study-specific documents, other than the signed consent, the participant will be referred to by the study participant number/code, not by name.

### **12.2. Access to Data**

Direct access will be granted to authorised representatives from the Sponsor and host institution for monitoring and/or audit of the study to ensure compliance with regulations.

### **12.3. Data Recording and Record Keeping**

All study data will be initially collected and entered onto a password protected Excel document and saved on a university computer that requires a user log-in.

Personal data will be recorded electronically on data forms that are entered into an access-restricted computer and encrypted. The participants will be identified by a study specific participant number in any database.

During the study, data containing personal information such as name of the participant and contact details will be stored securely with restricted user access. Personal information will be removed from study documents such as source documents as soon as practical, and then replaced with an ID number from a linkage document kept separately and securely. Documentation containing such personal information will be destroyed or de-identified 6-12 months after the end of the study.

Documents containing personal or identifying data such as the code break and consent forms will also be stored in cabinets with restricted user access during the study.

At the end of ethical approval, the study files will be archived in the Div. of Cardiovascular Medicine, University of Oxford for five years, after which time the custodian will agree a date for destruction and data will be destroyed confidentially.

Electronic data will be held on secure network drives/hard disks/ servers on password protected computers within locked offices. Backup copies of files will be made regularly weekly and stored on a different server/external hard drive. These back up locations will be subject to the same security principles as the primary locations. When datasets are complete, the primary copy will remain at the study site where it will be transferred onto optical media, e.g. DVD/external drive and undergo archiving for hard copy data. Any copies leaving the study site will be completely anonymised/de-identified.

Where participants have consented for storage and use of blood samples for future research, and further analysis beyond the end of the study as potential novel biomarkers are identified. The consent form will be retained for the life of the sample to meet HTA traceability requirements.

### **13. QUALITY ASSURANCE PROCEDURES**

The study may be monitored, or audited in accordance with the current approved protocol, GCP, relevant regulations and standard operating procedures. Data collected for the study may be reviewed for auditing and monitoring by authorised persons from the sponsor, regulatory authorities or their local host institutions to make sure that it is being carried out correctly. All investigators have a duty of confidentiality to research participants and nothing that could reveal their identity would be disclosed outside the research study team or site.

In addition, depending on the complexity, scale and risks inherent to the research study the quality assurance procedures may include a risk adaptive approach based on a formal risk assessment, planned monitoring activities (onsite and / or central monitoring) and the involvement of a number of study oversight committees.

#### **13.1. Risk assessment**

A risk assessment and monitoring plan will be prepared before the study opens and will be reviewed as necessary over the course of the study to reflect significant changes to the protocol or outcomes of monitoring activities.

#### **13.2. Study monitoring**

Regular monitoring will be performed according to the study specific Monitoring Plan. Data will be evaluated for compliance with the protocol and accuracy in relation to source documents. Following written standard operating procedures, the monitors will verify that the clinical study is conducted and data are generated, documented and reported in compliance with the protocol, GCP and the applicable regulatory requirements.

#### **13.3. Study Committees**

This study will include an independent safety monitoring committee which will consist of consultant cardiologist specialising in complex implantable cardiac devices and electrophysiology [REDACTED], and a consultant clinical oncologist specialising in the radiotherapy treatment of head and neck cancers [REDACTED]. This committee will routinely meet after the completion of each dose of the dose escalation protocol (see figure 2.), and dose escalation will only occur once the committee is satisfied with safety. In addition, if any SAE (as defined in section 10.2) is detected during study follow up visits, this will trigger a safety committee review. No further patients will be recruited and no further patients will receive radiotherapy pending outcome of this review.

